#### Pain

Pain and distress will assessed by obtaining: (1) the participant’s self-report of pain intensity using the Faces Pain Scale-Revised (FPS-R) (if participant is aged 3 years or over) [21]; (2) the parent’s report of the participant’s pain intensity using a Visual Analogue Scale-Pain (VAS-P) (alternatively, if participants are aged 8 years or over they will complete the VAS-P in lieu of the caregiver) [22]; (3) the nurse’s observational rating of the participant’s pain and distress using the Face, Legs, Activity, Cry, Consolability (FLACC) scale [23]; and (4) pulse and respiratory rates of the participant.. All four of these measures will be taken before and after dressing removal and before and after dressing application. Pulse and respiratory rates will be recorded once at each time point to provide an objective measure of pain and distress in participants, as increases in these physiological measures have been shown to be indicative of pain and distress [6,24] Any analgesic and/or sedative medication administered to the participant at each dressing change will also be recorded.

Face scales are particularly useful for obtaining self-report pain scores from younger children as they have been reported to be easier to follow than other types of self-report scales and are well-validated measures [25]. The FPS-R is clinically valid for a paediatric population and was chosen over other faces pain scales because of its psychometrically sound characteristics including the exclusion of smiling faces or tears, thus eliminating the possible confusion of pain intensity and affect by children [21]. The VAS-P is a valid and reliable self-report measure of acute pain in children over the age of 8 years [22]. The VAS-P is not valid for children under the age of 8, but is valid as a parent-report measure of pain and therefore parents and caregivers of these children in this study will instead score their child’s pain level [22]. The FLACC scale is a valid and reliable behavioural observer-report (nurse or health professional) measure of a child’s pain. Self-reports of pain intensity can be difficult to ascertain and inaccurate when a child is receiving sedative and analgesic medications or is too young to verbalise their pain level; therefore the use of the FLACC scale can be a suitable and accurate alternative [23].

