## Background

The ultimate goal of burn wound healing is to promote early closure as this has considerable influence on the long-term quality and appearance of a hypertrophic scar. It has been demonstrated that even scars considered small in size can contribute to negative psychosocial outcomes for children, hence the importance of effective wound healing techniques [1,2]. The relationship between scar formation and time taken to re-epithelialise in children is well understood by burn clinicians. According to Cubison and colleagues [3], partial thickness burns that re-epithelialise within the optimal time period of 10–14 days generally do so without scarring, and those taking more than 3 weeks will invariably scar. Burns re-epithelialising at between 2 and 3 weeks will have variable amounts of scar tissue laid down depending on many factors including skin type, anatomical location of the burn and age of the child [3].

Children whose burn wounds re-epithelialise at more than 3 weeks post-injury are at a high risk of residual or hypertrophic scarring [3]. Scar management therapy facilitated by occupational therapists to manage and prevent hypertrophic scarring currently involves the use of various types of silicone contact media, pressure garments and splints. Engagement in scar management therapy typically occurs for 18 months or until scars reach maturity. While these scar management techniques are successful for some children in managing scars, there are inevitably children who require ongoing treatment of their scar tissue as they grow older. Scars generally do not grow with the child, and if situated around a joint, can lead to joint contracture and loss of function, resulting in ongoing scar reconstruction to keep up with the child’s growing body [4]. Therefore the initial care of the burn wound and choice of burn dressing are vital in creating the ideal healing environment to ensure rapid re-epithelialisation of the wound and to avoid the possibility of hypertrophic scarring.

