### Data collection

Demographic information and clinical details will be obtained from the caregiver and the patient’s chart regarding the mechanism of the burn injury, site of the injury, total body surface area of the burn and first aid the patient received. Children over the age of 4 years will be given the Ditto™ (virtual reality) device (Diversionary Therapy Technologies, Queensland, Australia) to engage in the “Bobby got a Burn” procedural preparation story at their first dressing change. These children may also engage in a choice of games or stories on the Ditto™ during all dressing changes. At the first dressing change only, each participant will have their burn/s scanned using the LDI2-BI (VR) Laser Doppler Imager (LDI) (Moor Instruments, Axminster, Devon, UK), which measures wound depths (in blood perfusion units) as a percentage of total wound area. The laser Doppler imager scan will provide an objective assessment of burn depth to enable a comparison of treatment group demographics [19]. Participants who have burn wounds on different body parts will have separate scans completed for each body part involved. If burn wounds are circumferential or across curved areas, more than one scan will be taken at the frontal, lateral and medial aspects to obtain an accurate scan. In addition, blinded photo reviews of burn depth will be undertaken by a panel of burn specialists (consultants and nurses).

At each dressing change appointment, pain, behaviour and physiological measures (pulse rate and respiratory rate) will be taken before and after dressing removal and before and after the re-application of a new dressing. The time taken for the dressing removal, cleaning and re-application procedure, the number of nurses required to complete the entire procedure, quantity of dressings used and analgesia given to the participant will be recorded. A tracing of the wound using Visitrak™ grids (Smith & Nephew, Hull, UK) and a photograph using the 3D LifeViz Camera (Quantificare, Cedex, France) will be taken. Nursing staff treating the child will be surveyed on a 5-point Likert scale regarding the ease of use of the dressing for that particular child. Parents or caregivers and children over the age of 8 years will be surveyed on a 5-point Likert scale regarding their physical function while wearing the dressing.

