#### Data analysis

All statistical analyses will be conducted using SPSS 21 (IBM Corp., Armonk, NY, USA). Generalised linear models, estimating variance appropriately for repeated measures, will be used to determine whether there are differences among the Acticoat™ group, the Acticoat™ combined with Mepitel™ group and the Mepilex Ag™ group in primary and secondary outcomes. Changes in the intervention effects will be examined with burn depth, burn total body surface area, mechanism of injury, anatomical location of the burn, skin type, ease of dressing removal and application and physical function considered a priori to be of potential interest. All data will be analysed as intention to treat and on a per protocol basis, with the intention to treat analysis being the primary approach for this trial. Any missing data will be handled using the multiple imputation method. All tests will be two-tailed and only those with a *p* value <0.05 will be considered statistically significant.

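### The VAS-P changes from parent to child rater at age 8, and a distraction device is given only to children over 4, but age is not among the prespecified analysis factors

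*Protocol article*

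**What the plan says.** The Pain section of the protocol article lists four measures, each taken before and after dressing removal and before and after application.

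- **FPS-R:** the child's own report, collected from age 3.
- **VAS-P:** scored by the parent for younger children; "alternatively, if participants are aged 8 years or over they will complete the VAS-P in lieu of the caregiver". The reason given is that "The VAS-P is not valid for children under the age of 8, but is valid as a parent-report measure of pain".
- **FLACC:** "the nurse’s observational rating of the participant’s pain and distress using the Face, Legs, Activity, Cry, Consolability (FLACC) scale", with no age limit stated.
- **Pulse and respiratory rate:** no age limit stated.

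The Data collection section adds a second age rule: "Children over the age of 4 years will be given the Ditto™ (virtual reality) device", for a preparation story at the first dressing change. It continues: "These children may also engage in a choice of games or stories on the Ditto™ during all dressing changes".

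The inclusion criteria admit ages 0 to 15, so both boundaries fall inside the trial population. The Data analysis section compares the three arms with generalised linear models for repeated measures. It says that changes in the intervention effect will be examined with burn depth, burn surface area, "mechanism of injury, anatomical location of the burn, skin type, ease of dressing removal and application and physical function considered a priori". Age and VAS-P rater are not on that list. The Recruitment section describes randomisation by computer-generated random numbers in sealed envelopes and mentions no stratification by age.

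**The concern.** Below 8 the VAS-P records how much pain a parent thinks the child has. From 8 it records how much pain the child says they have. The protocol itself treats these as different uses of the scale, valid for different ages. If the two are analysed as one variable with no age term, any average gap between parent and child scoring becomes unexplained variance in the dressing comparison. The combined estimate is then also a mixture whose meaning depends on the age mix recruited.

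The device rule adds a second age-related source of variation. It may lower pain in children over 4, and this affects every pain measure.

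Pain is presented as a primary measure, and the Sample size section says the trial is large enough for it. Age must be known to establish eligibility, so it is available as a baseline variable at no cost. Because the article fixes its list of factors a priori, age added after the data are seen would no longer carry that status.

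**Working it through.** **The plan's own figure.** The Sample size section uses an SD of 4 days, a difference of 3 days, 80% power and α = 0.05; the Data analysis section makes tests two-tailed. The standardised effect is 3/4 = 0.75 SD.

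n per arm = 2 × (1.960 + 0.842)² × 4² / 3² = 27.9, rounded up to 28. Power at 28 is 0.801. The stated 28 per group is reproduced.

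The pain calculation cannot be reproduced, because no pain scale, SD or difference is given. I therefore carry over 0.75 SD at 28 per arm as a reference case only.

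**Assumed inputs (not in the article).**
- p, the share of children aged 8 or over: 0.1 to 0.4.
- d, the mean shift between child and parent VAS-P scoring, in within-rater SDs: 0.25 to 1.0.

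**Variance when age is left out.** The variance of the mixture is 1 + p(1 − p)d² times the within-rater variance. Power is Φ(0.75 × √(14 / factor) − 1.960), where 14 = 28/2.

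| p | d | Variance factor | Power at 28 per arm |
|---|---|---|---|
| no rater shift | 0 | 1.000 | 0.801 |
| 0.1 | 0.25 | 1.006 | 0.799 |
| 0.2 | 0.5 | 1.040 | 0.786 |
| 0.3 | 0.5 | 1.052 | 0.781 |
| 0.1 | 1.0 | 1.090 | 0.767 |
| 0.4 | 1.0 | 1.240 | 0.712 |

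For the last row: 1 + 0.4 × 0.6 × 1² = 1.24, then 0.75 × √(14/1.24) − 1.960 = 0.56, and Φ(0.56) = 0.712.

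**Chance imbalance in who rated.** The SD of the difference between two arms in the share aged 8 or over is √(2p(1 − p)/n).
- n = 28, p = 0.1: √(2 × 0.09/28) = 0.080.
- n = 28, p = 0.4: √(2 × 0.24/28) = 0.131.
- n = 33 (100/3): 0.074 and 0.121 for the same two shares.

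Simulating three arms of 28, some pair of arms differs by 15 percentage points or more in about 11% (p = 0.1) to 44% (p = 0.4) of randomisations. Multiplying the n = 28 SDs by d, the rater mix moves an arm contrast by a chance amount with SD between 0.25 × 0.080 = 0.02 and 1.0 × 0.131 = 0.13 within-rater SDs.

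The variance inflation and the chance imbalance are two views of the same cost and should not be added together. The device boundary at age 4 is not quantified, because the article gives no effect size for it and no age distribution.

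**The case against.** The case against has several sound parts.

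- **Bias.** A reader might infer that the pain comparison is biased. The documents do not support that. The rater and device rules are identical in all arms, arms are randomised, and care apart from the dressing is the same. Chance imbalance in age is ordinary sampling error, already reflected in an unadjusted standard error.
- **Scope.** A reader might infer that the whole pain objective combines scores of different meaning. Only the VAS-P changes rater. The FPS-R is always the child's report, and not collecting it under 3 does not alter what it measures. FLACC and the physiological measures have no age switch. The device may change pain, but it does not change what a score means.
- **Pooling.** The article never says parent and child VAS-P scores will be combined; it only fails to separate them. The list under Data analysis concerns effect modification, and covariates may be set in an analysis plan that is not shown.
- **The Background section.** It says scar formation varies "depending on many factors including skin type, anatomical location of the burn and age of the child". A reader might take this as the protocol naming age as a driver of pain and then dropping it. The sentence is about scarring in burns that heal between 2 and 3 weeks, so it does not show that.
- **Size.** The range rests on two assumed inputs and starts near zero.

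What remains is narrower. The protocol builds two age boundaries into how pain is measured and managed, then fixes a list of factors without age. That list includes ease of removal and application and physical function while wearing the dressing, both observed after randomisation, while a baseline variable that determines who scores the VAS-P is left out. Naming age now is worthwhile even if an unseen document might also do so.

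**Conclusion.** The point holds as a matter of precision and interpretability for the VAS-P, and to a lesser extent of precision for the other pain measures through the device rule. No systematic bias between dressings is expected.

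Under the assumed ranges (10–40% aged 8 or over, rater shift 0.25–1.0 SD), variance rises by about 0.6–24%. Power for a 0.75 SD effect at 28 per arm goes from 0.80 to between 0.80 and 0.71. At the low end the loss is negligible; at the high end it is about 9 percentage points. The age mix, the rater shift and the use of 0.75 SD for pain are all assumptions.

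The interpretive problem does not depend on these numbers: a single combined VAS-P estimate averages proxy and self-report in proportions set by whoever is recruited.

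**What to change.** In the Data analysis section, add age at randomisation as a prespecified baseline covariate in the pain models, in three bands cut at the protocol's own boundaries: up to 4, over 4 to under 8, and 8 and over. The top band absorbs the VAS-P rater switch, and the cut at 4 absorbs the average effect of the device rule. Age band is fixed before randomisation, so adjusting for it is safe; optional use of the device follows randomisation and should not be adjusted for.

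Present the VAS-P by rater (parent, child) as well as combined.

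The cost is two degrees of freedom and one extra table, using a variable already collected. A dressing-by-age-band interaction is not part of this fix. With three arms and three bands it needs four more degrees of freedom, and the older bands may hold few children per arm, so any such analysis should be labelled exploratory.

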### Secondary outcome measures

#### Physical function

A self-report of the participants’ ease of movement while wearing the dressing will be obtained using a 5-point Likert scale question from children over the age of 8 years or their caregiver at the first dressing change [26].

#### Grafting

A note will be recorded if a participant’s wound requires grafting. Data collection will cease on that date for the participant as different dressings are used for wounds that are grafted; however all data preceding that point will be included for analysis.

#### Infection

At each dressing change, the wound will be assessed clinically by the consultant. If the consultant deems an infection to be present, a swab will be taken from the wound for confirmation and identification.

#### Cost-effectiveness of dressings

At each dressing change, nursing time to apply the dressing, the amount and size of each dressing used, and any other resources required will be recorded and a cost-analysis will then be calculated. Additionally, dressings required for scar management will also be recorded and analysed.

#### Scar assessment

If further scar management treatment is required after full re-epithelialisation of the burn injury has occurred, a referral will be made by the treating consultant to the scar management clinic. At 3 months following full re-epithelialisation of the burn injury, a face-to-face follow-up will be completed with all participants to conduct a skin and/or scar review in conjunction with Occupational Therapy. An ultrasound scan (BT12 Venue 40 MSK, GE Healthcare) [19] will be taken of the burn area to measure the height of the scar, and digital and 3D photographs will also be taken. The Patient and Observer Scar Assessment Scale will also be completed with the child (if over the age of 6 years) and/or caregiver. All scar management resources used with the participant will be recorded for a cost-analysis. At 6 months post-full re-epithelialisation, the same measures will be repeated.

#### Burn centre staff perspectives on dressings

Nursing staff, consultants and occupational therapists from our burn centre will be surveyed regarding their opinions of the three dressings prior to the commencement of data collection. The survey questions will be standardised and consist of Likert scales, tick boxes with a selection of responses and additional space for comments regarding the dressings. Nursing staff will be surveyed again using the same questions after data collection has ceased to examine any changes in their perceptions of the dressings after using all three for an extended period of time.

### Blinding

The dressing used for each participant cannot be completely masked, as the Acticoat™ dressing stains the healthy skin around a burn wound brown. The expert panel of burn wound specialists will be blinded where possible; however the primary investigator and expert panel may still be able to deduce what dressing a participant received. The primary investigator will also be present when dressings are being applied and removed to obtain pain scores from the participant, caregiver and nursing staff, and will see which dressing is being used on the child. Wherever possible during data collation and analysis, treatment groups will be de-identified.

### Discontinuation/adverse events

The infection of the burn wound is a potential adverse effect of any of the burn dressings. Infection rates at our burn centre are extremely low; however if any adverse effects such as infection occur, participants will only have data collected up until that point in time analysed, as clinical care (including dressing type) may change to address the adverse event. Additionally, if a consultant feels that a particular dressing is not appropriate for a participant’s care, they may change to a different dressing. If this occurs, data collection for this participant will cease from this date. All data preceding this date will be included for analysis.

### Statistics

#### Sample size

The primary outcome measure will be days until wound re-epithelialisation. Previous data in paediatric burn patients demonstrated re-epithelialisation within 15 (SD = 4) days and a minimally clinically important difference is 3 days [6]. Thus sample size was calculated at 28 per group at 80% power with an α of 0.05. Allowing for 20% loss to follow-up, a total of 100 participants will be required. The burn centre treats 800 children per year with burns so recruitment for this study should be achievable within 1 year. This sample size will also be adequate to find a significant difference in data collected from pain scores, powered on data from a previous study [6].

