**Methods/Design:**

Children aged 0 to 15 years with an acute partial thickness (superficial partial to deep partial thickness inclusive) burn injury and a burn total body surface area of ≤10% will be eligible for the trial. Patients will be randomised to one of the three dressing groups: (1) Acticoat™ or (2) Acticoat™ combined with Mepitel™ or (3) Mepilex Ag™. A minimum of 28 participants will be recruited for each treatment group. Primary measures of pain, distress and healing will be repeated at each dressing change until complete wound re-epithelialisation occurs or skin grafting is required. Additional data collected will include infection status at each dressing change, physical function, scar outcome and scar management requirements, cost effectiveness of each dressing and staff perspectives of the dressings.

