### Primary outcome measures

#### Days to re-epithelialisation

The number of days from the burn injury date until wound re-epithelialisation occurs, surface area of the wound and percentage of wound re-epithelialisation will be calculated by four methods: (1) clinical judgement from the consultant; (2) use of Visitrak™ grids; (3) 3D camera photographs and analysis on specialist computer software; and (4) blinded review of the 3D photographs by a panel of burn specialists (consultants and nurses).

The 3D photographs and Visitrak™ tracings will be taken of a participant’s burn wound at every dressing change. A ruler will be included in all 3D photographs for measurement calibration in the associated software package Dermapix™ (Quantificare, Cedex, France). The 3D photographs will be analysed by the primary investigator on the Dermapix™ software programme to calculate the burn wound surface area and area of re-epithelialisation of the wound from each dressing change. The Visitrak™ will also be used to trace around total burn area and re-epithelialised areas of the burn wounds at each dressing change in order to calculate wound surface area and percentage of re-epithelialisation.

A blinded review of the 3D photographs will be undertaken by a panel of burn wound specialists (consultants and nursing staff) who will assess the progress of re-epithelialisation and appearance of each participant’s burn wound after data collection has been completed.

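### The protocol names one primary outcome for sample size but lists pain and distress as primary elsewhere, with one unadjusted 0.05 threshold, so the primary false-positive rate exceeds 5% by an amount the text does not fix

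*Protocol article*

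**What the plan says.** Under Statistics, Sample size, there is a single primary outcome: "The primary outcome measure will be days until wound re-epithelialisation". The 28 per group is derived from it (SD 4 days, difference 3 days, 80% power, α 0.05). The same paragraph says, without figures, that this number also suffices for pain scores.

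Two other places say something different:

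- The Abstract (Methods/Design) is plural: "Primary measures of pain, distress and healing will be repeated at each dressing change until complete wound re-epithelialisation occurs".
- The section Primary outcome measures has two entries. Under Days to re-epithelialisation, the time to healing, "surface area of the wound and percentage of wound re-epithelialisation will be calculated by four methods": consultant judgement, Visitrak tracing, 3D photographs with software, and a panel review of the photographs. Under Pain there are four items: FPS-R, VAS-P, FLACC, and pulse with respiratory rate. Of these it says: "All four of these measures will be taken before and after dressing removal and before and after dressing application".

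No healing method, pain scale or time point is named as the one that decides.

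The Data analysis section looks for "differences among the Acticoat™ group, the Acticoat™ combined with Mepitel™ group and the Mepilex Ag™ group in primary and secondary outcomes", using models that allow for repeated measures. Its decision rule covers all tests: only those with a p "value <0.05 will be considered statistically significant".

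**The concern.** Which outcome is primary is a matter for the protocol, and this one gives two incompatible answers in current text. The hypothesis under Study design covers both healing and pain, so pain cannot be dismissed as background. If the Abstract and the Primary outcome measures section are followed, several results can each be reported as the trial's primary answer, each tested at 0.05.

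The measures are also not interchangeable. FPS-R applies only from age 3, the VAS-P rater changes from parent to child at age 8, and FLACC is scored by the nurse. The healing methods run from the treating consultant's judgement to a panel whose blinding, by the Blinding section, is only partial. They can disagree, and so can healing and pain. The headline could then be chosen after the data are seen, and the 5% error rate would not hold.

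**Working it through.** **1. The plan's own figure.** Inputs from Sample size: difference 3, SD 4, two-sided α 0.05, power 80%.

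n per group = 2 × (1.960 + 0.842)² × 4² / 3² = 27.9, so 28. This reproduces the stated number. It is a calculation for one outcome in a two-group comparison at the full 0.05. Power at 28 per group is 80% by the normal approximation (79% by t-test).

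**2. Chance of at least one false positive, independent tests.** For k tests at 0.05 the chance is 1 − 0.95^k.

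| Reading of the primary set | k | Chance |
|---|---|---|
| Sample size section alone, one three-group test | 1 | 5% |
| One healing test and one pain test | 2 | 1 − 0.95² = 9.75% |
| Healing once, four pain measures | 5 | 1 − 0.95⁵ = 22.6% |
| Four healing methods, four pain measures | 8 | 1 − 0.95⁸ = 33.7% |

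Counting pulse and respiratory rate separately makes the last row nine tests and 37.0%.

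**3. Allowing for correlation.** The document gives no correlations, so these are assumed values. Each measure gets one three-group test (2 degrees of freedom), simulated with no true differences.

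| Tests | Assumed correlation | Chance |
|---|---|---|
| Healing once + 4 pain | pain measures 0.3 to 0.7, none with healing | about 22% down to 18% |
| 4 healing + 4 pain | 0.3 / 0.5 / 0.7 within each set, none between | 32% / 29% / 25% |
| 4 healing + 4 pain | healing 0.90-0.95, pain 0.3-0.7, none between | about 20-25% |
| All eight | 0.5 between every pair | about 25% |
| All eight | 0.9 between every pair | about 12% |

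**4. Cost of the alternatives at 28 per group** (difference 3, SD 4, two-group normal approximation). The standardised difference is 3 / (4 × √(2/28)) = 2.806.

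- At 0.05: Φ(2.806 − 1.960) = 80%.
- At 0.025, the first step of Holm with two primaries: Φ(2.806 − 2.241) = 71% (69% by t-test).
- At 0.05/8 = 0.00625, Bonferroni over eight: Φ(2.806 − 2.734) = 53% (49% by t-test). Restoring 80% would need 46 per group (48 by t-test).

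**The case against.** The best case on the other side has four parts.

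- **The four healing methods are four ways to measure the same wound.** Nothing says that each will have its own test, and methods applied to one wound are likely to agree closely. The Abstract names pain, distress and healing, not eight measures. This stands. A reader might infer that the false-positive rate simply is 25-34%, but that needs eight separate tests and limited correlation, and the document states neither.
- **Repeated pain assessments need not multiply the tests.** Data analysis specifies models for repeated measures, so the four time points per dressing change can enter one model per measure. This also stands. A reader might infer that each time point adds a test, or that unadjusted pairwise comparisons among the three arms raise the rate further. The text states neither; it speaks of differences among the three groups.
- **A multiplicity procedure, a lead scale and a rule for discordant results are often left to the analysis plan, which is not shown.** This is fair, and their absence alone would be no finding. The point rests instead on two conflicting statements of what is primary, together with a stated threshold for all tests.
- **Pain and healing have equal place in the aim and hypothesis, and the trial is registered, ethics-approved and recruiting.** Demoting pain is therefore more than an edit. This stands as a cost, and it is why an option that keeps both is given below.

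**Conclusion.** The contradiction is real and should be resolved. The Sample size section has one primary outcome; the Abstract and the Primary outcome measures section have more, with no lead measure. Under the stated 0.05 rule for all tests, 5% holds only if Sample size is read alone with a single three-group test.

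On every other reading the rate is higher, but no single figure belongs to this plan:

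- 9.75% for one healing and one pain test, if independent;
- about 18-23% for healing once plus four pain measures;
- about 20-34% for eight separate tests, if pain is uncorrelated with healing;
- about 12% if all eight are correlated at 0.9.

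The zero correlation between pain and healing is itself an assumption, and the Background argues that the two are linked. The finding that the rate exceeds 5% does not depend on which of these readings is chosen. The particular percentage does.

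**What to change.** Make the Abstract and the Primary outcome measures section agree with Sample size:

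1. Days to re-epithelialisation is the only primary outcome, judged by one named method of the four listed. The other three are supportive. It is tested by one three-group test at 0.05.
2. Pain is the key secondary outcome, using one measure and one summary over time that the sponsor names before data lock. It is tested at 0.05 only if the primary is significant.
3. All remaining measures are reported without confirmatory claims.

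This restores 5% for the primary result and leaves 28 per group unchanged. Pain loses equal standing with healing. Because the trial is registered, approved and recruiting, the change should be made as a dated amendment before the data are locked. The 28 was derived for two groups, so power for the three-group test should be stated too. With 84 children analysed it is about 69% if the arm means are evenly spaced over 3 days, and about 82% if one arm differs from the other two by 3 days.

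If the sponsor keeps healing and pain as two primaries, name one measure for each and use Holm across the two. The power for healing should then be restated as about 71% (normal approximation, 28 per group) in the worst case, where pain is not significant and healing must be met at 0.025.

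### A total of 100 children does not leave the required 28 per group after the planned 20% loss; 20% needs 105, and 100 covers 16% (minor)

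*Protocol article*

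**What the plan says.** The Sample size section names days to re-epithelialisation as the outcome on which the trial is sized. It takes its planning values from earlier paediatric data that "demonstrated re-epithelialisation within 15 (SD = 4) days", and adds that "a minimally clinically important difference is 3 days". From these it concludes: "Thus sample size was calculated at 28 per group at 80% power with an α of 0.05". The next sentence gives the enrolment figure: "Allowing for 20% loss to follow-up, a total of 100 participants will be required". The step from 28 per group to 100 is not written out.

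Three other statements bear on the calculation. The Data analysis section says "All tests will be two-tailed" and "Any missing data will be handled using the multiple imputation method". The Methods/Design part of the abstract says "Patients will be randomised to one of the three dressing groups" and "A minimum of 28 participants will be recruited for each treatment group". No allocation ratio is stated; a single figure per group implies equal allocation.

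**The concern.** An allowance for loss to follow-up is there so that the number left after the expected loss still meets the number that the power calculation needs. Here the need is 3 × 28 = 84. Because the lost fraction is taken from those enrolled, the need has to be divided by one minus that fraction. Adding 20% to the need itself gives too small a total. The printed 100 sits close to the second calculation and not to the first.

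What is at stake is whether the stated power holds under the loss that the protocol itself plans for. The three printed figures (28 per group, 20% loss, 100 in total) cannot all stand together. The figure of 28 has no slack to absorb the difference, because it is the unrounded requirement of 27.9 taken up to the next whole number.

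**Working it through.** **Inputs.** From the Sample size section: SD 4 days, difference 3 days, power 80%, α 0.05, 28 per group, 20% loss, total 100. From the Data analysis section: two-sided tests. From the abstract: three groups, taken here as equal in size.

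**1. Reproduce the 28.** Normal approximation for two means:

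n = 2 × [4 × (1.960 + 0.842) / 3]² = 27.9, rounded up to 28 per group.

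This matches the protocol. The 28 is therefore the number needed for one unadjusted two-group comparison, before any loss. Three groups need 3 × 28 = 84.

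**2. Look for the source of the 100.**

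- 84 × 1.2 = 100.8, close to the printed 100 (strictly it rounds up to 101).
- 84 / (1 − 0.2) = 105, which is 35 per group.

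**3. Apply the stated loss to the stated total.**

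- 100 × 0.8 = 80 children, and 80/3 = 26.7 per group, against the 28 required.
- Largest loss that still leaves 84: 1 − 84/100 = 16%.
- Check of the alternative: 105 × 0.8 = 84, or 28 per group.

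**4. Effect on power** (difference 3, SD 4, two-sided α 0.05, one pair of groups, no adjustment for multiple comparisons):

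| Evaluable per group | Normal approximation | t test |
|---|---|---|
| 28 | 80.1% | 78.7% |
| 26.7 | 78.2% | 76.6% |
| Change | −1.9 points | −2.1 points |

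**5. Effect on the detectable difference** (80% power, normal approximation):

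- At 28 per group: 4 × (1.960 + 0.842) × √(2/28) = 3.00 days.
- At 26.7 per group: 4 × (1.960 + 0.842) × √(2/26.67) = 3.07 days.

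**The case against.** The strongest reply is that the effect is trivial. A change of 0.07 day in the detectable difference is under two hours, while wounds are assessed at dressing changes 3 to 4 days apart. That stands, and it is why the point is minor. It does not make the printed figures agree.

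A second reply is that multiple imputation, with intention to treat as the primary analysis, keeps all randomised children in the analysis. This does not rescue the figure. The protocol chose to allow for 20% loss when it set the total, and imputation does not in general restore the information lost with an unobserved outcome.

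A third reply is that the inflation formula is not shown, so nobody can say that 20% was simply added. That is correct, and the additive route is only the likely explanation. The inconsistency does not depend on it, because 80% of 100 is less than 84 however the 100 was reached.

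Three stronger readings are tempting, and the protocol supports none of them:

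- A reader might infer that the abstract contradicts the Sample size section, because it attaches the 28 to recruitment. It gives a minimum, and 100 enrolled is about 33 per group, which meets it. The wording is loose, but the two statements are compatible.
- A reader might go on to infer that recruitment could stop at 84 and leave about 22 per group after losses. That is not the plan: the Sample size section says plainly that 100 are required.
- A reader might set the t-test figure of 76.6% against the promised 80% and charge the whole gap to the allowance for loss. By the t test, 28 per group already gives 78.7%, so part of that gap comes from using the normal approximation. Only about 2 points belong to this error.

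**Conclusion.** The point holds as an internal inconsistency in the Sample size section. Under the protocol's own loss rate, the total of 100 falls 4 evaluable children short of 84, or 5 short in enrolment terms (105 − 100). The stated 80% power is not delivered at 20% loss; on the method that reproduces the 28 it is about 78%. Severity is minor: the mistake is clear, its consequence is small, and it changes no conclusion about design or feasibility.

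The conclusion assumes equal group sizes, loss spread evenly across groups, an SD of 4 days, and children lost to follow-up contributing no information on healing time. The power figures describe one unadjusted comparison of two groups. Whether that is the right basis for sizing a three-group trial is a separate question, which neither 100 nor 105 settles.

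**What to change.** Make one of these changes in the Sample size section:

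- Keep 100 and state that it allows for about 16% loss to follow-up.
- Keep 100 and 20% loss, and state that 80 evaluable children give about 78% power for a 3-day difference, or 80% power for 3.07 days. Say that this is the normal approximation for one unadjusted two-group comparison.
- Keep 20% loss and 80% power, and correct the total to 105 (35 per group).

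Show the formula in each case. Optionally, label the 28 in the abstract as the evaluable number per group, so that it is not taken for an enrolment target.

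The first two options cost only wording. The third costs five more children, at a centre that the protocol says treats 800 children with burns a year.
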